**Figure 1 F1:**
[figure not shown]
Schedule of enrolment, interventions, and assessments.

**Figure 2 F2:**
[figure not shown]
Flow-chart of the protocol.

Before the enrolment, patients will read the information and sign the informed consent at the OUC, ISI of Milan, Italy under the supervision of [name]. Participants’ information collected will be confidential.

### Sampling

3.2

Since the study is focused on saliva samples, subjects with severe hypo-salivation at the first sampling (saliva flow rate at baseline <0.1 mL min^−1^), because of their inability to dissolve the tablet formulation, will be rolled out. Saliva production will be determined by the spit method at baseline (*t* = 0) and after 7 days of treatment (*t* = 1) with Salifluss^TM^ twice a day or placebo.

The participants will be asked to avoid oral hygiene practices including flossing, brushing, and mouth-rinses as well as eating, and drinking for at least 2 hours before collection. Before sampling, the mouth will be rinsed with water for 2 minutes, and the subject will be asked to wait for 10 minutes.

The saliva samples will be obtained in the morning (8.00 am–10.00 am) according to the circadian rhythms in salivary flow.^[11]^ The unstimulated saliva samples will be collected by expectorating into sterile 50 mL tubes every 30 seconds. for 5 minutes as described earlier.^[12]^ The stimulated saliva will be collected in the same way after 2 minutes of chewing a paraffin wax ball.

The samples collected by an operator unaware of clinical data will be weighted, the pH will be measured by a pH-sensitive electrode, then centrifuged at 5000 *g* for 10 min at 4°C; the obtained supernatants will be supplemented with EDTA-free Protease Inhibitor Mixture (Sigma–Aldrich, Dorset, UK) and stored al −80° for the QP analysis. The collected samples will be analyzed at the Department of Pharmaceutical Sciences “Pietro Pratesi,” University of Milan, Milan, Italy (DISFARM) research laboratory.

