## Introduction

1

The pH of the oral cavity (OC) is a synthetic parameter that underlies a multifactorial process of continuous adjustment including the effect of saliva^[1]^ as a buffer and the contribution of the OC microbiome.^[2]^ In some diseases of the OC an impairment of these adjustment mechanisms is supposed to alter the normal flow of saliva and, consequently, the pH and the oral microbiome (OM)^[3]^ with the expansion of potentially pathogenic strains such as the most cited streptococcus viridans.^[4]^

Carnosine (Car) is an endogenous dipeptide, composed of β-alanine and l-histidine, that was originally discovered in larger amounts in skeletal muscle of some vertebrates, including humans, showing a greater dependence on non-oxidative forms of energy metabolism.^[5]^ This peculiar association with muscular tissue and its pH-buffering properties has led to associate Car with the intracellular acid-base homeostasis of muscles.^[6]^ More recently, the physiological role of Car has been expanded beyond the intracellular buffering properties, supporting a role in sarcoplasmic Ca^2+^ regulation and neutralization of reactive oxygen species (ROS). It is well known that ROS induce the formation of reactive electrophilic carbonyl species by reacting with lipids and sugars which, in turn, react with proteins forming irreversible adducts (AGEs, ALEs, and EAGLEs) and cross-links that may affect the cardiovascular wall matrix that becomes less distensible, especially during the aging process and/or diseases.^[7]^ Thus, it is thought that Car and, indeed, other histidine-containing peptides, may prevent chronic diseases via their anti-inflammatory, anti-oxidative, anti-glycating, anti-ischaemic, and chelating properties.^[8]^ Furthermore, the localization of Car in other tissues such as the brain, olfactory bulb, heart, stomach, pancreas, kidney has suggested further potential uses in preventing, for example, neurodegenerative disorder and cognitive function or the development of type II diabetes.

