## Aim of the study

2

The main objectives of this protocol are to estimate the quantity/quality of oral salivae and OM in healthy volunteers and in subjects affected by common OD, before and after 7 days of treatment with Salifluss^TM^, 1 tablet twice a day. The characteristics of oral saliva (Sal) that will be studied are (a) unstimulated and stimulated (paraffin-activated) salivary flow rates and pH and (b) quantitative proteomics (QP), on selected targets, representing the main proteins/components of OM.

By matching Sal characteristics with OM and comparing them with OD, we do expect to elucidate their mutual relationship; furthermore, using specific bioinformatics tools to analyze the data, before and after treatment with Car, we are looking to see its potentials on preventing/treating OD and, using QP, eventually elucidate the mechanism of action.

The study will take place at the Odontoiatric University Clinic (OUC), Istituto Stomatologico Italiano (ISI) of Milan, Italy, in a prospective, randomized, double-blind, and placebo-controlled fashion.

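### Excluding subjects on t = 0 flow truncates the baseline healthy–diseased comparison of flow on its own endpoint; the randomised treatment contrast is not biased

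*Protocol article*

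**What the plan says.** Section 2 (Aim of the study) words its main aim as follows: "estimate the quantity/quality of oral salivae and OM in healthy volunteers and in subjects affected by common OD, before and after 7 days of treatment". The saliva characteristics listed there include "unstimulated and stimulated (paraffin-activated) salivary flow rates and pH", and the same section adds: "By matching Sal characteristics with OM and comparing them with OD, we do expect to elucidate their mutual relationship". Flow before treatment, in healthy controls (Cs, 20) and diseased subjects (Ds, 40), is therefore one of the quantities to be estimated and compared.

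Section 3.2 (Sampling) makes t = 0 the baseline measurement. It also provides that "subjects with severe hypo-salivation at the first sampling (saliva flow rate at baseline <0.1 mL min^−1^), because of their inability to dissolve the tablet formulation," are excluded. The sentence opens with a remark that the study is centred on saliva samples. Both unstimulated and stimulated saliva are collected, but the rule gives one threshold and does not say which flow it uses.

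Section 3.5 (Statistical analysis) defines the primary outcome as the treatment-related change in the saliva parameters. It is analysed by ANCOVA with treatment and baseline value in the model.

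**The concern.** The rule selects on a variable that the study also wants to describe. Its main stated reason concerns the tablet, and a t = 0 flow needs no tablet. By the time the rule can be applied, the flow has already been measured. Removing those subjects cuts the lower tail from both flow distributions, and it cuts more from whichever group has more subjects there.

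The Introduction says that in some oral diseases "an impairment of these adjustment mechanisms is supposed to alter the normal flow of saliva". If the alteration is a reduction, more Ds than Cs fall below the cut-off and the observed Cs–Ds difference in flow is too small. The subjects lost would be those with the most extreme flow, who are informative for the saliva–disease relationship in Section 2.

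A separate problem is the undefined flow measure: a subject may pass on one flow and fail on the other, so eligibility is not fixed by the text.

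**Working it through.** **Stated figures.** The article gives no flow distribution and no share of subjects below 0.1 mL/min, so there is no figure of its own to reproduce. It supplies only the cut-off (0.1 mL/min) and the group sizes (20 Cs, 40 Ds). Every median, mean and SD below is an assumption.

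**Step 1: effect on the Cs–Ds mean difference, equal log-SD.** For log-normal flow with median m and log-SD s:

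- z = (ln 0.1 − ln m)/s
- share excluded = Φ(z)
- mean before = m·exp(s²/2)
- mean after = mean before × [1 − Φ(z − s)]/[1 − Φ(z)]

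Example with s = 0.6:

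- Ds, m = 0.2: z = (−2.303 + 1.609)/0.6 = −1.155. Excluded 12.4%; mean 0.2394 → 0.2625.
- Cs, m = 0.4: z = −2.310. Excluded 1.0%; mean 0.4789 → 0.4831.
- Difference 0.2394 → 0.2206, a loss of 7.9%.

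The same calculation with Cs median 0.4 throughout:

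| log-SD | Ds median | Cs excluded | Ds excluded | Difference before | After | Loss |
|---|---|---|---|---|---|---|
| 0.4 | 0.20 | 0.03% | 4.2% | 0.2167 | 0.2111 | 2.6% |
| 0.4 | 0.35 | 0.03% | 0.1% | 0.0542 | 0.0540 | 0.3% |
| 0.6 | 0.20 | 1.0% | 12.4% | 0.2394 | 0.2206 | 7.9% |
| 0.6 | 0.30 | 1.0% | 3.4% | 0.1197 | 0.1142 | 4.6% |
| 0.8 | 0.20 | 4.2% | 19.3% | 0.2754 | 0.2465 | 10.5% |
| 0.8 | 0.30 | 4.2% | 8.5% | 0.1377 | 0.1268 | 7.9% |

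The log-ratio loses more (10% to 28% for log-SD 0.6–0.8 and Ds medians 0.2–0.3), but Section 3.5 does not name that scale.

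**Step 2: size against sampling error.** The standard error of the difference is √(varC/20 + varD/40), with var = mean²·(exp(s²) − 1). For s = 0.6 and Ds median 0.2 this is √(0.0994/20 + 0.0248/40) = 0.075. The shift of 0.019 is 0.25 of one standard error, the largest ratio in the table.

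**Step 3: sensitivity to the spread assumption.** Here SDs are set on the raw scale, still log-normal.

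- Means 0.5 and 0.4, SD 0.2 in both: 0.3% of Ds excluded; difference 0.100 → 0.099.
- Means 0.3 and 0.2, SD 0.15 in both: 24% of Ds and 1.8% of Cs excluded; difference 0.100 → 0.063, a 37% loss.
- Equal means 0.4, SD 0.15 in Cs and 0.30 in Ds: difference 0 → −0.014.
- Cs 0.40 (SD 0.15), Ds 0.42 (SD 0.35): difference −0.020 → −0.039, away from zero.

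Neither the direction nor the size is fixed without knowing the two distributions.

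**Step 4: the randomised contrast.** I simulated 4,000 ANCOVAs in Ds, 30 active and 10 placebo, with every baseline at or above 0.1. Baseline was log-normal (mean 0.25, SD 0.15), and the outcome was 0.1 + 0.6 × baseline + effect + error (SD 0.1). For a true effect of 0.080 the mean estimate was 0.079. The simulation error is roughly 0.1 × √(1/30 + 1/10)/√4,000 = 0.0006, so the gap is under two simulation errors. With no effect, the type I error was 5.2%. The rule introduces no bias there.

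**The case against.** **The primary outcome is untouched.** Section 3.5 targets change under treatment, and a pre-treatment cut-off applied alike to both arms does not bias it. This stands in full, and it confines the point to the baseline description.

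**The direction is not documented.** A reader might infer that the rule removes mainly Ds and pulls the Cs–Ds difference towards zero. The Introduction speaks only of altered flow in some diseases and does not say lower. Step 3 shows the opposite movement with unequal spread, so attenuation holds only conditionally.

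**The effect may be tiny.** Section 3.1 restricts diseased subjects to ages 18–40, takes age-matched controls, and excludes smoking, drug treatment and systemic disease. Flows below 0.1 mL/min may be rare. This stands, but the article gives no share either way.

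**There is a sample-based reason too.** The rule's opening words refer to saliva samples. If the cut-off is on unstimulated flow, a 5-minute collection below it yields under 0.1 × 5 = 0.5 mL, which may limit pH and proteomic work. This stands for those measures. It does not stand for flow, because a low flow is itself a valid value.

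**Exclusion from the baseline description is a reading.** The text does not say that the t = 0 value is discarded, the flow-chart is not available here, and analysis sets are often left to a fuller document. That is fair. Still, Section 3.2 makes no provision for keeping the value, and its plain sense is that these subjects leave the study.

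**Conclusion.** The concern holds in a limited form. The baseline healthy–diseased comparison of flow is selected on its own endpoint, and the tablet reason does not require giving up a flow already measured. If Ds flow is lower with similar spread, the difference is attenuated; otherwise the direction is open.

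With equal log-SD of 0.4–0.8, Cs median 0.4 and Ds median 0.2–0.35, the loss in the mean difference is 0.3% to 10.5%, at most about a quarter of a standard error. A lower-flow scenario with equal raw SD reaches 37%, but only by placing 24% of Ds below the cut-off. No figure in the article favours one scenario.

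The rule should not be read as a threat to the randomised result: it restricts that result to subjects with baseline flow of at least 0.1 mL/min. The unspecified flow measure is a defect whatever the distributions. Overall severity is minor to moderate.

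**What to change.** - Apply the existing cut-off to entry into the randomised treatment phase only.
- Keep the t = 0 flow of every consented subject in the baseline Cs–Ds comparison, or at least in a sensitivity analysis. Keep pH and the stored sample where the volume allows.
- Report the number below the cut-off separately for Cs and Ds.
- State whether the cut-off refers to unstimulated or stimulated flow. The article does not settle this, so the sponsor must.
- State that the treatment effect applies to subjects at or above the cut-off.

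The cost is protocol wording and a slightly larger baseline set. No extra procedure is needed, since the t = 0 sample is already taken. The downside is that the baseline set then differs from the randomised set, so each table must name the set it uses.

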### Administration of Car

3.3

Subjects understudy will be instructed to assume Salifluss^TM^ twice a day, in the morning and before bedtime. Salifluss^TM^ is a Class I medical device according to EU Dir. no 93/42/CE (as amended by EU Dir. No. 2007/47/CE), notified to Italian Ministry of Health with ID number 1810197/1810202. At recommended doses, the intake quantities of the substances meet the requirements and limitations set by the Italian Ministry of Health. As previously introduced, Salifluss^TM^ is a 400 mg mucoadhesive oral tablet (13 × 4 mm^2^) with smooth surfaces whose main ingredient is Car. The tablet should be placed in the gingival fornix and, thanks to its mucoadhesiveness, let to dissolve slowly. The dissolution time of the tablet is around 2 hours in normal salivation conditions. Placebo tablets, similar to Salifluss^TM^ ones, will be administered to randomly selected n = 20 subjects, 10/10 from Cs/Ds. An SMS reminder will be sent to all the subject reminding to take the pill.

Patients will be encouraged to report any adverse events and other unintended effects of trial interventions.

Attached the technical and safety data sheets, the certificate of analysis, and the sell-sheet of the extract of Cr.

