The OM is a relevant part of the whole human microbiome since it contains several different niches, with distinct microbial communities, colonizing the OC, including not only bacteria but also fungi, viruses, archaea, and protozoa. These communities form a complex ecological system that influences OC and systemic health. Indeed the prevalent oral diseases (OD), namely dental caries and periodontal diseases, are believed to be microbiota-related. Furthermore, several evidences support the theory that many systemic diseases are associated with an altered OM, among these the most frequently associated diseases are metabolic, such as diabetes, cardiovascular and oncological ones.^[9]^ For their prevalence worldwide, among OD, periodontal infections, including gingivitis and chronic periodontitis, are possibly the most prevalent human microbial diseases (HMD).^[10]^

To protect the OC from HMD, in the present project we chose Car as a possible preventive and/or therapeutic principle for its aforementioned multiple biological effects. Thus, we decided to test the safety and efficacy of Salifluss^TM^ (Metis Healthcare s.r.l., Milano, Italy) a 400 mg mucoadhesive oral tablet (13 × 4 mm), that recognize Car as the main ingredient, on healthy volunteer and in subjects affected by common OD.

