### Subjects selection

3.1

Among subjects referring to the OUC, we will enroll, on a voluntary basis, n = 40 diseased subjects (Ds), aged 18–40 years having at least 1 of the following OD: (a) dental erosions, (b) caries, and (c) périodontopathies, for example, gingivitis or aggressive/chronic periodontitis.

The criteria for each OD were defined on the basis of commonly accepted grading scores in dentistry. Dental erosions will be counted; for caries, we will adopt the missing and filled dental criteria; for périodontopathies, we will record the probing depth, clinical attachment loss, plaque index, and bleeding on probing using a manual periodontal probe.

A complete medical and dental history will be obtained from all participants; all the volunteers must not present allergies/intolerances to the consumption of Car or take other food supplements or any type of drug treatment (interview). Exclusion criteria will be also smoking, pregnancy/lactation, and the presence of any systemic diseases such as cardiovascular and respiratory, diabetes mellitus, HIV infection, or inflammatory conditions causing non-plaque dependent OD. Patients eligible for the study will return to the OUC after being pre-screened. Before being enrolled in the study, participants will provide written and informed consent for use of their saliva samples and clinical data for scientific research purposes. The study is in accordance with the guidelines of the World Medical Association Declaration of Helsinki.

A control group (Cs) of 20 age-matched subject with periodontal health will be enrolled among the staff of the OUC. The number of subjects identified and considered sufficient for the research is based on a preliminary test conducted on the salivary flow obtained from the staff involved in the project. The schedule of enrolment, interventions, and assessments, and the flow-chart of the protocol are depicted in Figures 1 and 2.

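### The article says it will test safety, but names no safety objective or outcome, and the only harms method it states is volunteered reporting

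*Protocol article*

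**What the plan says.** - **Introduction (section 1):** the authors write that "we decided to test the safety and efficacy of" the tablet, in healthy volunteers and in people with common oral diseases.
- **Aim of the study (section 2):** "The main objectives of this protocol are to estimate the quantity/quality of oral salivae and OM in healthy volunteers" and in diseased subjects, before and after 7 days of treatment. Safety is not listed. The section describes the trial as randomized, double-blind and placebo-controlled.
- **Administration of Car (section 3.3):** "Patients will be encouraged to report any adverse events and other unintended effects of trial interventions". The tablet adheres in the gingival fornix and is used twice a day; "The dissolution time of the tablet is around 2 hours in normal salivation conditions". Placebo goes to 20 randomly selected subjects, 10 from each group.
- **Subjects selection (section 3.1):** "n = 40 diseased subjects (Ds), aged 18–40 years", plus 20 controls drawn from clinic staff.
- **Sampling (section 3.2):** saliva is taken at baseline and again after 7 days, by an operator who is kept from the clinical data.
- **Statistical analysis (section 3.5):** the primary outcome is change in saliva parameters, in subjects with adequate samples at both times. Missing samples are removed whatever the cause, and non-compliance is given as an example. No harms outcome or summary is named.

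**The concern.** A safety test is declared once and then not carried into the objectives or the stated outcome. The stated way of gathering harms depends on the participant taking the initiative. With this kind of local exposure the plausible effects are mild and in the mouth, and people often do not mention such effects unless asked.

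Two features of the design add to this. The arms contain different proportions of clinic staff and clinic attenders, so any difference in how readily the two groups report would enter a pooled arm comparison. In addition, the only analysis set the article describes requires adequate samples before and after treatment. Someone who stops because the tablet is unpleasant could fall out of that set, and a tolerability table built on it would lose the people it most needs.

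At stake is how a paper with few or no reported events could be read. Without a uniform enquiry, such a result would be weak support for a statement about safety.

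**Working it through.** The article gives no adverse-event rate, safety sample size or safety power, so there is no figure of its own to reproduce. Event rates and capture shares below are assumptions, shown as ranges.

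**1. Numbers by arm (sections 3.1 and 3.3).**
- Total: 40 Ds + 20 Cs = 60. Placebo: 10 Cs + 10 Ds = 20.
- Active: (20 − 10) Cs + (40 − 10) Ds = 10 + 30 = 40.
- Share of Cs: active 10/40 = 25%; placebo 10/20 = 50%.

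**2. What zero events would show.** The exact one-sided 95% upper bound is 1 − 0.05^(1/n).

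| Group | n | Bound at zero events |
|---|---|---|
| All active | 40 | 7.2% |
| Active Ds | 30 | 9.5% |
| All placebo | 20 | 13.9% |
| Active Cs, placebo Cs or placebo Ds | 10 | 25.9% |

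The two-sided version for n = 40 is 8.8%. These bounds depend on n alone and take every event as captured.

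**3. Effect of incomplete reporting.** If a share c of affected subjects report, the chance of at least one report among 40 is 1 − (1 − c × p)^40, where p is the true rate. With no reports, the upper bound on the true rate becomes 7.2%/c.

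| Assumed capture c | P(≥1 report), p = 5% | P(≥1 report), p = 10% | Bound on true rate, 0/40 reported |
|---|---|---|---|
| 100% | 87.1% | 98.5% | 7.2% |
| 75% | 78.3% | 95.6% | 9.6% |
| 50% | 63.7% | 87.1% | 14.4% |
| 25% | 39.5% | 63.7% | 28.9% |

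**4. Effect of the unequal mix.** With no treatment effect, the pooled active-minus-placebo difference is (0.75 − 0.50) × (Ds reporting rate − Cs reporting rate). Assume 30% in Ds and 10% in Cs:
- Active: 0.25 × 10% + 0.75 × 30% = 25%.
- Placebo: 0.50 × 10% + 0.50 × 30% = 20%.
- Spurious difference: 5 percentage points. It disappears when arms are compared within Cs and within Ds.

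**5. What full capture would buy.** Fisher exact power at 40 against 20 subjects (two-sided 0.05) is 26% for 20% vs 5%, 64% for 30% vs 5%, and 67% for 40% vs 10%. For 30% vs 5%, it falls to 43%, 16% and 1% at capture of 75%, 50% and 25%. Uniform questioning improves the description of common local effects, but formal comparison stays weak.

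**The case against.** The strongest reply is that this is a condensed article. The assessment schedule is in a figure that is not shown, and the full protocol may hold an event form or a harms table. That stands: one can say only that volunteered reporting is the sole method this article states. An instruction to report also does not rule out a question at the day-7 visit. It does not remove the mismatch in the text, where a safety test is declared in one section and absent from the objectives and the outcome in two others. Section 2 speaks of main objectives, so safety could be a secondary one, but then it should be named.

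The reply is also right about several stronger inferences a reader might draw:
- **That the safety question cannot be answered at all.** Volunteered events in a randomized, double-blind, placebo-controlled trial carry some comparative information, though imprecise.
- **That healthy volunteers fall outside the reporting instruction because it speaks of patients.** Section 3.5 uses that word for the analysed subjects of both groups, and the consent text in section 3.1 gives no separate wording for controls.
- **That there is no denominator by arm.** The planned numbers are fixed at 40 and 20. The open issue is which subjects a tolerability table would count.
- **That the 7.2% bound measures the reporting defect.** It reflects sample size and would be the same after structured questioning. The larger bounds rest wholly on assumed capture shares.

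That mild local effects go unreported, and that staff and attenders report differently, are judgements; the documents do not establish either. Finally, having the saliva operator put the questions would give that person clinical information that section 3.2 keeps from them, so the remedy must avoid it.

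**Conclusion.** The point holds in a limited form. The article's safety claim is not matched by its objectives or its outcome, and its stated harms method is a poor fit for mild local effects of a mucoadhesive tablet. Under-counting is likely but cannot be sized from the documents: at a true rate of 5%, the chance of any report among 40 active subjects runs from 87.1% with full capture to 39.5% with an assumed 25% capture. The imbalance in group mix follows directly from the allocation; the 5-point example depends on assumed reporting rates. The text does not support saying that safety cannot be assessed or that controls are excluded from reporting. This should be corrected, and because the Discussion says the study has not started, it still can be. It does not threaten the saliva outcomes.

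**What to change.** Reconcile sections 1, 2, 3.3 and 3.5 in one of two ways.

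1. **Drop the safety claim** from the Introduction and keep volunteered reporting as general oversight.
2. **Keep it as 7-day tolerability**, named as a secondary outcome:
   - Give all 60 subjects, Cs and Ds, the same short self-completed form at the existing day-7 visit, with a fixed list of local oral events and one open question.
   - Have it completed after saliva collection, while treatment is still masked, and not seen by the saliva operator.
   - Tabulate counts by arm within Cs and within Ds, over all treated subjects and not only those with adequate samples. Seek the form from those who stop early as well.
   - Where no events are seen, report the exact upper confidence bound (7.2%, one-sided 95%, for 0/40) and make no claim beyond it.

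The cost of the second option is one short form, one table and a few lines of text, with no extra visit. More minor events will be recorded than under volunteered reporting. The results should be presented as descriptive, since 40 against 20 subjects does not give a powered safety comparison.
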